## Abstract

**Background:**

Multiple Sclerosis is an autoimmune inflammatory disease of the central nervous system that often leads to premature incapacity for work. Therefore, the MSnetWork project implements a new form of care and pursues the goal of maintaining or even improving the state of health of MS patients and having a positive influence on their ability to work as well as their participation in social life. A network of neurologists, occupational health and rehabilitation physicians, psychologists, and social insurance suppliers provide patients with targeted services that have not previously been part of standard care. According to the patient’s needs treatment options will be identified and initiated.

**Methods:**

The MSnetWork study is designed as a multicenter randomized controlled trial, with two parallel groups (randomization at the patient level with 1:1 allocation ratio, planned *N* = 950, duration of study participation 24 months). After 12 months, the patients in the control group will also receive the interventions. The primary outcome is the number of sick leave days. Secondary outcomes are health-related quality of life, physical, affective and cognitive status, fatigue, costs of incapacity to work, treatment costs, out-of-pocket costs, self-efficacy, and patient satisfaction with therapy.

Intervention effects are analyzed by a parallel-group comparison between the intervention and the control group. Furthermore, the long-term effects within the intervention group will be observed and a pre-post comparison of the control group, before and after receiving the intervention in MSnetWork, will be performed.

**Discussion:**

Due to the multiple approaches to patient-centered, multidisciplinary MS care, MSnetWork can be considered a complex intervention. The study design and linkage of comprehensive, patient-specific primary and secondary data in an outpatient setting enable the evaluation of this complex intervention, both on a qualitative and quantitative level. The basic assumption is a positive effect on the prevention or reduction of incapacity for work as well as on the patients’ quality of life. If the project proves to be a success, MSnetWork could be adapted for the treatment of other chronic diseases with an impact on the ability to work and quality of life.

**Trial registration:**

The trial MSnetWork has been retrospectively registered in the German Clinical Trials Register (DRKS) since 08.07.2022 with the ID DRKS00025451.

## Background

Multiple sclerosis (MS) is a chronic inflammatory autoimmune disease of the central nervous system that affects more than 223,000 statutorily insured people in Germany [1]. The disease is usually diagnosed between the ages of 20 and 40 and is associated with severe physical, cognitive, and social impairments [2]. Treatment options are defined in guidelines and focus on recovery from attacks, slowing down the disease progression and managing MS symptoms [3]; by now there is no known cure for MS.

For many MS patients, the disease leads to a significant reduction in their working ability. As a result, the proportion of patients with part-time jobs, disability pensions, or premature retirement increases in the course and severity of the MS [2]. Disease-specific factors such as mobility limitations, fatigue, and cognitive impairments are primarily responsible here. Comorbid depression, which is often accompanied with MS, also frequently leads to restrictions on the ability to work. However, working conditions also have an impact on employment prognosis, as in many cases there is a lack of understanding in physically demanding activities in the workplace and a lack of necessary flexibility to ensure the (continued) employment of people with MS [4]. This is precisely where the MSnetWork project comes in because it is less about the effect of individual measures or interventions on clinical disease parameters (e.g. relapse frequency), but rather about the effect on participation in private, social, and, in particular, vocational life and the associated long-term securing of the ability to work.

The MSnetWork project implements a new form of care and pursues the goal of maintaining or even improving the state of health of MS patients and having a positive influence on their ability to work as well as their participation in social life. A network of neurologists, occupational and rehabilitation physicians, psychologists, and social insurance suppliers provides patients with targeted services that have not previously been part of standard care and are directly tailored to the personal needs of the patients. According to the patient’s needs based on a systematic and regular assessment of functional capacity, the following treatment options will be identified, initiated, and coordinated by the neurologist:participation-oriented care by the MS-specialized neurologist,occupational health examination by an occupational physician,psycho-social and legal counseling from a qualified person,disease education by a neuropsychologist or a neurologist who is specialized in MS,MS-specific outpatient and inpatient rehabilitation by a rehabilitation physician.

Risks of loss of social participation as well as of inability to work will be identified and should be reduced by the interventions. The patient will be empowered to make informed decisions about their treatment options and will be supported in upholding the ability to work and to participate in social life.

The study was initiated by the Professional Association of German Neurologists (Berufsverband Deutscher Neurologen e.V., BDN) and is conducted together with GWQ ServicePlus AG as representative of a large number of statutory health insurance funds and the Professional Association of German Occupational Physicians (Verband Deutscher Betriebs- und Werkärzte e. V.). The University of Greifswald (UG) and the Institute for Community Medicine of the University Medicine of Greifswald (UMG) are responsible for the scientific and economic evaluation within MSnetWork.

## Methods / design

### Research questions and working hypotheses

The main aims of the study are (a) to improve or stabilize the health status of patients with MS and (b) to prevent or reduce their incapacity to work. Therefore, the intervention consists of a portfolio of measures to improve the coordination of specialist care as well as the early integration of socio-medical, occupational, psychosocial, rehabilitative, and health care services.

### Study design

The MSnetWork study is designed as a multicenter randomized controlled trial (RCT), with two parallel groups. The duration of study participation is 24 months. The patients are consecutively enrolled between January and December 2022, and assigned to an intervention group or a control group in a ratio of 1:1 after checking the inclusion and exclusion criteria. After 12 months, the patients in the control group will also receive the intervention measures, during the first 12 months they receive standard care. The study procedure planned is shown in Fig. 1.

**Fig. 1 Fig1:**
[figure not shown]
Interventions and timeline

The intervention effect is analyzed as follows:Essentially, the intervention effect is carried out by analyzing the course of the primary and secondary outcomes in the intervention and control groups in the first 12 months (parallel-group comparison).In the following 12 months, the intervention group continues to receive the intervention. Further analyses of the outcome variables in this time are particularly important to be able to check the stability of this effect over the time (long-term) to see if an effect of the intervention is present after the first 12 months.The control group receives the intervention in the second half of the study period. The course of the primary and secondary outcomes in the control group between the first and second period (months 0 to 12 vs. months 13 to 24) will be analyzed either. Such a pre-post comparison is methodologically weaker than a parallel group comparison, but it offers the possibility to examine the effect of the intervention once again from an independent perspective.

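### The within-arm course in months 13–24 cannot by itself show whether the effect lasts, fades or grows, because it mixes background drift with change in effect

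*Protocol article*

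**What the plan says.** Under Study design (text with Fig. 1), the protocol article sets out three analyses.

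- The main one follows the outcomes "in the intervention and control groups in the first 12 months (parallel-group comparison").
- The second concerns year 2 of the intervention arm: "In the following 12 months, the intervention group continues to receive the intervention", and analyses in this period are "particularly important to be able to check the stability of this effect over the time (long-term"), that is, to see whether an effect is present beyond month 12.
- The third is a pre-post comparison within the control arm. The article itself describes this as weaker than a parallel-group comparison.

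The Abstract (Methods) locates the second analysis in a single arm: "Furthermore, the long-term effects within the intervention group will be observed". The control arm is no longer untreated by then: "After 12 months, the patients in the control group will also receive the intervention measures".

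The Background describes a worsening course: "the proportion of patients with part-time jobs, disability pensions, or premature retirement increases in the course and severity of the MS". Primary outcome names both 12 and 24 months for sick leave days.

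**The concern.** An effect is a difference from what would have happened without the intervention. After month 12 no randomised arm shows that. The year-2 question is nevertheless to be answered from the course of outcomes in the intervention arm, and the article names no comparator for it.

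Sick leave in that arm can move between years for reasons unrelated to the intervention, such as disease course or calendar trends in sick leave. Even the direction is open. Days may rise as MS worsens, or fall as patients leave work and stop accruing sick leave (an inference from the Background, not a statement in it).

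The article states the weakness of a before-after reading only for the control arm. The intervention-arm reading has the same weakness and carries no caveat. What is at stake is the long-term conclusion and the interpretation of the 24-month time point of the primary outcome.

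**Working it through.** **Inputs from the documents.** Mean of 25 days per year; target difference of 5 days; two-sided 0.05; power 80%; 1:1 allocation; gross N = 950; 20% dropout over the first 12 months; 30% or 50% of patients with zero days (all Sample size, allocation also in Study design). No drift, no standard deviation and no year-2 dropout are given.

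**Step 1: the plan's own figures.** 600 / 0.8 = 750 and 860 / 0.8 = 1,075. Both reproduce. They concern the 12-month comparison only; nothing is sized for months 13–24.

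**Step 2: what the within-arm change measures.** Let D be the background drift from year 1 to year 2, E1 the year-1 effect and E2 the year-2 effect in the intervention arm. Then

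within-arm change = D + (E2 − E1).

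This is one observed quantity with two unknowns. For illustration take an untreated mean of 25 days in year 1 and E1 = −5, so the arm's year-1 mean is 20. Its year-2 mean is 25 + D + E2. All D values are assumptions. The last column is explained in Step 3.

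| D | E2 | Year-2 mean | Within-arm change | Year-2 difference between arms |
|---|---|---|---|---|
| 0 | −5 (kept) | 20 | 0 | 0 |
| +5 | −10 (doubled) | 20 | 0 | −5 |
| −5 | 0 (lost) | 20 | 0 | +5 |
| +5 | −5 (kept) | 25 | +5 | 0 |
| 0 | 0 (lost) | 25 | +5 | +5 |

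A change of 0 fits three different truths, and a change of +5 fits two.

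**Step 3: the randomised contrast in months 13–24.** Let F be the delayed-start arm's effect in its first year of intervention. The difference is

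(25 + D + E2) − (25 + D + F) = E2 − F.

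Drift cancels. The last column of the table uses F = −5, that is F = E1. If this equality fails, the reading fails too: with E2 = −2.5 (half lost) and F = −2.5, the difference is 0 although the effect has halved. With no effect in either arm (E2 = F = 0), the difference is also 0. So the contrast needs the 12-month result beside it, and it cannot show an effect against no intervention.

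**Step 4: its precision, on assumptions.** Take 950 × 0.8 = 760, or 380 per arm, with no further dropout. For the standard deviation use a zero-inflated Poisson with overall mean 25 and zero share p: λ = 25/(1 − p), variance = 25(1 + pλ).

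- p = 0.3: λ = 35.7, SD = 17.1. Standard error = 17.1 × √(2/380) = 1.24; 95% half-width = 1.96 × 1.24 = 2.4 days.
- p = 0.5: λ = 50, SD = 25.5. Standard error = 25.5 × √(2/380) = 1.85; 95% half-width = 1.96 × 1.85 = 3.6 days.

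Power, as Φ(difference / standard error − 1.96), is 98% and 77% for full loss of the 5-day effect, and 52% and 27% for loss of half (2.5 days).

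**Step 5: the matched non-participants.** With drift D′ in the matches, the change in intervention-arm patients minus the change in their matches is D + (E2 − E1) − D′. This equals the change in effect only if D′ = D, which matching supports but randomisation does not guarantee.

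**The case against.** The best defence is that the design text does not restrict the year-2 analyses to one arm; only the Abstract does, and its verb is descriptive. Patient outcomes run to month 24 without restriction by arm (Table 2). Statistical analyses says the models can test group, time, period and interaction effects. Secondary outcomes describes a propensity-matched cohort of non-participants. The exact contrast could sit in a fuller document. This stands in part: the tools for a better answer exist. But none of these places assigns a comparator to the stability question, and the one sentence that locates the analysis puts it within the arm.

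Four stronger readings are tempting, and the documents do not support them.

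- A reader might infer that the trial claims persistence after the intervention ends. It does not; the text says the arm continues to receive it.
- A reader might put the drift at, say, 10–20% of 25 days, or 2.5–5 days, which is 50–100% of the 5-day effect. The article gives no annual rate, and the Background speaks of part-time work, pensions and retirement, not sick leave days. Such figures only illustrate.
- A reader might take a year-2 difference near zero as proof of a lasting effect. Step 3 shows why it is not.
- A reader might think the main result is weakened. The effect is essentially assessed over the first 12 months, and the sample size rests on that.

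**Conclusion.** The point holds for the long-term conclusion only. A within-arm course in months 13–24 cannot by itself distinguish a lasting, fading or growing effect, and the article gives this caveat for the control arm but not for the intervention arm. That follows from the structure of the comparison and needs no assumed drift. How far a conclusion could be wrong cannot be stated, because the documents give no drift.

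The randomised 12-month comparison is unaffected. A better answer is available within the planned design, but it is limited. The between-arm contrast rests on equal first-year effects in the two arms and, on the assumed standard deviations and 380 per arm, would often miss partial waning. This is a worthwhile, inexpensive improvement, not a fault in the primary analysis.

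**What to change.** 1. Label the intervention arm's course in months 13–24 as descriptive, with the same caveat as the control arm's pre-post comparison, and describe any conclusion as concerning continued intervention.

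2. Add, without replacing anything, the randomised contrast between arms in months 13–24: second against first year of intervention, over the same calendar time. Report it with its confidence interval. Read it as evidence on waning only together with the 12-month effect and under the stated assumption that the delayed-start arm's first-year effect equals that of the early-start arm. State that it cannot show the presence of an effect against no intervention.

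3. For claims outcomes available in the matched non-participants, add the year-1 to year-2 change in intervention-arm patients minus that in their matches, labelled non-randomised. The article describes this cohort under treatment costs and frequency, so sick leave days would have to be included in its extract. Participants enrolled by direct treatment contract, without a health insurer, would not contribute.

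The cost is a little more analysis, possibly one added variable in the matched extract, and a narrower long-term claim with limited power for partial waning.

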### Subjects and eligibility criteria

Criteria for study inclusion comprise the following: (1) patients with a confirmed diagnosis of multiple sclerosis; (2) patients of working age (aged 18–65 years); (3) patients employed (part-time or full-time) or in study or vocational training.

Criteria for study exclusion comprise the following: (1) patients with MS who are no longer of working age (older than 65 years); (2) patients who are unable to work; (3) patients with severe impairment of independence (corresponds to care level 4 and 5 in German social law), and (4) patients with severe mental disorders.

### Sample size

The calculation of sample size was done for the analysis of the primary outcome “number of sick leave days” per patient within 12 months. The calculation assumes that the difference in sick leave days is to be an average of 5 days (or 20% of the average sick leave days for MS patients in Germany) between the intervention and the control group. This number is deduced from the German statistics on types of illness [5], with an annual average number of 25 days of incapacity to work due to MS among the statutorily insured persons. Further, based on a database analysis of the insurances taking part, up to 50% of the insured persons with MS do not have any days of incapacity to work in a 12-month observation period. Hence, the number of cases is calculated with a regression model for count data with “zero inflation”.

Depending on the assumption about the proportion of insured persons without sick leave days (30% vs. 50%), with a statistical power of 80%, and a 2-sided significance level of 0.05, the minimum sample size necessary to identify a group difference for the primary outcome of sick leave days is between 600 and 860. An expected drop-out of 20% in the course of the twelve-month comparison period leads to an increase in the net case numbers to the gross case numbers of *N* = 750 and *N* = 1075 (Table 1).

**Table 1 Tab1:** Results of the calculations for determining sample size

Patients without days of incapacity to work within 12 months (in %)	Net number of cases	Gross number of cases^a^
30% 50%	600 860	750 1.075

^a^Drop out of 20% in 12 months

Therefore, we aim for an initial gross sample size of 950 cases in total (475 cases per group). This number of cases is somewhat closer to the upper limit and would thus make it possible to achieve the planned power even if the actual conditions deviate from the assumptions made.

The strategies to achieve adequate recruitment to reach the target sample size had been.

based on the number of patients being treated in the past in the neurological practices who would have fulfilled the eligibility criteria. Neurological practices will be identified with the help of the BDN, the Professional Association of Neurologists.

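### Planned size of 950 gives about 75% power, not 80%, in the protocol's own 50%-zero scenario, so the unqualified robustness sentence is wrong as written

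*Protocol article*

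**What the plan says.** All of this stands in the Sample size section of the protocol article and its Table 1.

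- The target effect: "the difference in sick leave days is to be an average of 5 days (or 20% of the average sick leave days", set against "an annual average number of 25 days of incapacity to work due to MS".
- The test: "with a statistical power of 80%, and a 2-sided significance level of 0.05".
- The share of patients with no days: the insurers' database shows that "up to 50% of the insured persons with MS do not have any days of incapacity to work in a 12-month observation period". Two values, 30% and 50%, are carried into the calculation.
- The result: "the minimum sample size necessary to identify a group difference for the primary outcome of sick leave days is between 600 and 860", the lower figure for 30% zeros and the upper for 50%.
- Drop-out of 20% over the 12-month comparison raises these to 750 and 1,075 enrolled.
- The decision: "we aim for an initial gross sample size of 950 cases in total (475 cases per group"). The protocol notes that this lies nearer the larger of the two enrolment figures and concludes that it "would thus make it possible to achieve the planned power even if the actual conditions deviate from the assumptions made".

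**The concern.** The conclusion does not follow from the table above it. A number nearer to 1,075 than to 750 is still below 1,075, so it cannot deliver 80% power where 1,075 are needed. The 50% share is also not a departure from the assumptions: it is one of the two assumptions, and the only share for which the section cites data. The sentence therefore presents a compromise between two scenarios as a reserve beyond them.

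At stake is the only power statement for the primary outcome. If about half the patients have no sick leave days and drop-out is as expected, the chance of missing a true 5-day difference is about 25% rather than the 20% that the text implies.

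**Working it through.** **Inputs, all from Sample size and Table 1:** two-sided 0.05; power 80%; net requirement 600 (30% zeros) and 860 (50% zeros); drop-out 20%; planned enrolment 950.

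**1. Reproduce the protocol's enrolment figures.** Gross = net / (1 − drop-out).
- 600 / 0.8 = 750
- 860 / 0.8 = 1,075

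Both match Table 1 exactly.

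**2. Apply the same rule to 950.**
- Net: 950 × 0.8 = 760
- Against the 50% scenario: 860 − 760 = 100 net short (100/860 = 11.6%), or 1,075 − 950 = 125 gross short
- Against the 30% scenario: 760 − 600 = 160 net to spare

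The shortfall needs nothing beyond Table 1.

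**3. Power at 760.** The net figures are taken as the protocol's own 80% anchors, and the expected test statistic is assumed to grow with the square root of the sample size:

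Power = Φ[(z₀.₉₇₅ + z₀.₈₀) × √(n / n₈₀) − z₀.₉₇₅], with z₀.₉₇₅ + z₀.₈₀ = 2.802 and z₀.₉₇₅ = 1.960.

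- 50% zeros: Φ[2.802 × √(760/860) − 1.960] = Φ(0.674) = 75.0%
- 30% zeros: Φ[2.802 × √(760/600) − 1.960] = Φ(1.19) = 88.4%

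As a cross-check, the standard deviation that makes 860 the 80% size for a 5-day difference in a plain two-mean comparison is 26.17 days. Power with 380 per group is then again 75.0%. This confirms the arithmetic; it is not independent evidence.

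**4. Sensitivity to drop-out at 50% zeros.**
- 80% power needs 860 of 950 analysable: 1 − 860/950 = 9.5% drop-out at most, under half of what the protocol expects.
- At 25% drop-out, 950 × 0.75 ≈ 712 remain and power is about 72%.

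**5. Where 760 stops being enough.** Table 1 gives only two points, so this is interpolation.
- Linear: 30 + 20 × (760 − 600)/(860 − 600) = 42% zeros
- Holding the number of patients with at least one day constant: 600 × 0.7 = 420 and 860 × 0.5 = 430, so 1 − 430/760 = 43% to 1 − 420/760 = 45%

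**What could not be checked.** The net figures of 600 and 860 cannot be re-derived, because the article gives no dispersion. Steps 1, 2 and the 9.5% limit in step 4 do not depend on it. The power figures take whatever dispersion is already built into Table 1.

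**The case against.** The best defence is that the sentence is cautious and largely true. It speaks of making the planned power possible, the text does not call 950 the upper limit, and 1,075 is printed just above, so nothing is hidden. Read as a margin over the 30% scenario, the claim holds: power there is about 88%, drop-out could reach 1 − 600/950 = 37% before power falls below 80%, and at 20% drop-out the interpolated limit of 42–45% zeros covers more than half of the 30–50% range. The database figure is a ceiling, and it describes insured persons with MS, whereas Subjects and eligibility criteria restricts the trial to people in work, study or training. Choosing a size between two bounds is a legitimate decision.

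Most of this stands. A reader might infer from the shortfall that 50% zeros is the expected case, that 950 is simply too few, or that the robustness claim is false throughout. The documents support none of these: 50% is given as an upper value, the share that applies to the trial population is not shown, and moderate departures from 30% are covered.

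What the defence does not rescue is the lack of any limit. The sentence sets no bound on the deviation, and it fails at a value that the protocol itself planned for. Printing 1,075 nearby does not qualify a conclusion that contradicts it. Nor is this a detail left to a fuller document: it is a statement made in the text and contradicted by the adjoining table.

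**Conclusion.** The point holds in a limited form. With 950 enrolled and 20% drop-out, the trial exceeds its stated power at 30% zeros (about 88%) and falls about 5 percentage points short at 50% zeros (about 75%). The unqualified statement that the planned power is achieved even under deviation is wrong as written.

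That 760 is below 860 follows from Table 1 alone. The 75% and 88% rest on square-root-of-n scaling from the protocol's own anchors, a standard approximation and not a run of its zero-inflated model. The 42–45% limit is an interpolation between two points and should not be quoted as a computed result.

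A reader might go further and infer that a null result would be over-interpreted. Nothing in the article says how planned power would be used in reading the result, and a 5-point gap at the upper end of the range does not carry that conclusion. Sample size, primary outcome, analysis model and type I error are untouched; what needs correcting is the justification.

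**What to change.** Keep 950 and replace the robustness sentence with:

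*950 gross (760 net after 20% drop-out) gives about 88% power at 30% zeros and about 75% at 50% zeros; 80% power at 50% zeros would require drop-out of at most about 9.5%.*

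If a limiting zero share for 80% power is wanted as well, either label 42–45% as interpolated from Table 1 or recompute it with the zero-inflated model used for the original calculation.

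The cost is one sentence and no extra patients or design change. The only drawback is that the stated power looks slightly less favourable. The alternative, keeping the claim of 80% power at 50% zeros with 20% drop-out, would take 1,075 enrolled, 125 more than planned.
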